## Abstract

**Background:**

Eating disorders are serious psychiatric illnesses that are often associated with poor quality of life and low long-term recovery rates. Peer mentor programs have been found to improve psychiatric symptoms and quality of life in other mental illnesses, and a small number of studies have suggested that eating disorder patients may benefit from such programs. The aim of this study is to assess the efficacy of a peer mentor program for individuals with eating disorders in terms of improving symptomatology and quality of life.

**Methods:**

Up to 30 individuals with a past history of an eating disorder will be recruited to mentor 30 individuals with a current eating disorder. Mentoring will involve 13 sessions (held approximately every 2 weeks), of up to 3 h each, over 6 months.

**Discussion:**

This pilot proof-of-concept feasibility study will inform the efficacy of a peer mentoring program on improving eating disorder symptomatology and quality of life, and will inform future randomised controlled trials.

**Trial registration:**

Australian and New Zealand Clinical Trials Registration Number: ACTRN12617001412325. The date of registration (retrospective): 05/10/2017.

**Electronic supplementary material:**

The online version of this article (10.1186/s40814-018-0268-6) contains supplementary material, which is available to authorized users.

## Background

Eating disorders are serious psychiatric conditions with high rates of morbidity and mortality. They are associated with a staggering socioeconomic cost of almost $70 billion per year in Australia alone [1]. Anorexia nervosa is associated with the most serious consequences, having the highest death rate of any mental illness, with one in ten of those diagnosed dying as a result of the physical effects of starvation or suicide [2, 3]. The efficacy of treatments for eating disorders is limited, often resulting in suboptimal recovery and high relapse rates. Anorexia nervosa, specifically, is associated with long-term recovery rates of less than 50% among surviving patients [4, 5]. The complex nature of eating disorders demands an innovative and specialised solution to positively impact on relapse and recovery rates. Research has shown that maintaining social connections and applying life skills can support recovery in eating disorders and other mental illnesses (e.g. [6, 7]); yet, little research has been undertaken in the eating disorders field, particularly in relation to peer support programs.

Peer support is based on the belief that people who have faced, endured and overcome adversity can offer useful support, encouragement, hope and mentorship to others facing similar situations [8]. In broad terms, peer work can be classified into three categories [9]: self-help which involves voluntary peer support, self-referral and often independent and autonomous groups; consumer operated which refers to establishments where consumers run the organisation; and integrated which involves either voluntary or paid peer work that is positioned within existing mental health or related organisations and services. Most peer work in Australia sits within an ‘integrated’ category, where peer workers operate within existing mental health services, often working as team members alongside mental health workers.

Mental health peer work is a relatively new approach to service delivery. Evaluation has lagged behind implementation of peer workforce roles; however, a number of randomised controlled trial findings are available, and although the evidence base is a developing one, there is a strong indication that a substantial peer workforce in a psychiatric service will improve patient outcomes [10]. Peer mentor programs, which encompass support programs delivered by individuals typically in recovery from an illness to those with a current diagnosis, have been found to reduce hospital readmission rates in a range of mental health issues. For example, a study by Sledge et al. [6] utilised a mixed sample of psychiatric patients and found that those assigned a peer mentor had significantly fewer re-hospitalisations and shorter stays in hospital than patients who did not participate in the program. It has been noted in the literature that peer workers themselves can be both positively and negatively affected by providing peer support. This is an important and underexplored area. In a study specifically examining the impact of mentoring programs on people with eating disorders, Perez et al. [7] reported improved quality of life and family relationships, and improvements in psychological, emotional and physical wellbeing in individuals matched with a mentor. In this program Mentor Connect, the mentor-mentee relationship aimed at supporting the mentee to try new skills and work towards recovery-based goals [7]. Cardi et al. have a trial in progress at present assessing the use of peer support in the SHARED (Self-Help And Recovery guide for Eating Disorders) trial [11]. Other than these early evaluations, very little evidence is yet available in the literature to support peer mentoring in eating disorders [12].

A recent systematic review and synthesis of the impact of peer support on eating disorders yielded only four eligible studies (*N* = 270*)* [13]. One such study, which evaluated a mentoring program for women with eating disorders [7], reported that quality of life and treatment compliance were significantly increased in matched (*n* = 58) compared to unmatched (*n* = 49) mentees. In another study, an 8-week mentoring pilot program for undiagnosed (subclinical) adolescent girls (*n* = 31) demonstrated a significant reduction in disordered eating by the conclusion of the program [14]. In a qualitative study included in the review [15], mentees reported feeling understood, ‘normal’ and inspired, as a result of sharing with someone who had been through the same experience. A major theme that Fogarty et al. [13] identified from the synthesis of the above studies was the sense of belonging mentees experienced through the development of the mentoring relationship. Developing supportive relationships and an increased sense of belonging have been identified as an important aspect of eating disorder treatment [16], and these factors have been found to impact positively upon motivation for recovery [17]. Indeed, one study reported that recovered individuals attributed much of their recovery to aspects outside of formal therapy and placed particular emphasis on interpersonal relationships [18].

Potential benefits to the mentees’ recovery process notwithstanding, the feasibility of the current peer mentoring program relies on the delivery of mentoring that is sustainable and non-maleficent from the point of view of the mentors. It is therefore important to examine and analyse the likely risks and benefits associated with the provision of mentoring from this perspective, as these individuals are likely to have vulnerabilities associated with their previous diagnosis [19]. The peer mentoring literature in the broader mental health domain has identified several benefits that exist for mentors, including increased confidence, validation of their own recovery [20] and stable employment [21, 22]. However, it is unclear whether these benefits can be generalised to individuals who have recovered from an eating disorder.

There is little available research on the evaluation of risks to recovered individuals working in a mental health peer support role. In the literature that does exist, boundary issues and transgressions are cited as common challenges encountered by mentors [23–25]. Specifically, issues of confidentiality, multiple relationships, role confusion [26] and relational vulnerability due to self-disclosure [19, 25] have been identified as potential risks to the wellbeing of mentors. In a qualitative study investigating benefits and limitations of employing recovered individuals to deliver mental health services, mentors commonly reported they experienced stress associated with mentoring unmotivated or uncooperative mentees and highlighted the importance of adequate supervision and training [22]. Finally, the risk of relapse is important to examine, because if a relapse of an active mentor occurred, it would not only be (evidently) detrimental to the mentor, but it could also undermine the process of instilling hope in the mentee [25].

The examination of potential risks and benefits to mentors in this particular pilot program through both qualitative and quantitative data collection methods will attempt to assess whether the recruitment, training and support currently in place are effective and sufficient to ensure the wellbeing of the mentors, which is of paramount importance when considering the long-term feasibility of the program.

Previous peer mentoring programs in Victoria, Australia, have focused on a range of mental illnesses, though none have focused on people with eating disorders to date. In this context, we describe here a peer support program for people with an eating disorder, aimed at addressing a service gap in Victoria, Australia, for those who require additional support to sustain recovery while living independently.

### Study AIMS

The aim of this study is to determine the efficacy of a peer mentor program for people who have received eating disorder treatment in a specialist hospital setting or equivalent, in improving eating disorder symptomatology and quality of life, to inform future randomised controlled trials. An additional aim is to determine the feasibility of the study by assessing participants’ capability to complete the mentoring sessions and the program. The study’s feasibility will be measured in terms of having a sufficient number of participants sign up, participate and be retained until the end of the study and also that they tolerate and accept the intervention, that the intervention can be delivered as per protocol and that there are no concerning adverse events related to the study. The current program is a new program that combines peer support principles with documented evidence, balanced against available resource and organisational risk constraints. The program is designed to harness the experience of people who have recovered from eating disorders and combine it with regular de-briefing and supervision. This project aims to ensure eating disorder patients leaving hospital can better sustain their recovery outcomes in the long term. This is the first time such a program has been offered in Victoria, Australia. Thus, the primary aim of the study is to evaluate the effectiveness of the peer mentor program on eating disorder patient outcomes. A secondary, exploratory aim of the program is to evaluate the effects of the program on peer mentors in terms of eating disorder symptomatology and quality of life.

### Primary hypotheses

Participation in the peer mentor program is hypothesised to improve eating disorder symptomatology and quality of life, and reduce relapse rates in eating disorder participants (i.e. ‘mentees’, also referred to as ‘participants’ in appendices).

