## Methods/design

### Study design and mentor-mentee matching

The study is a multi-site collaborative trial conducted at Eating Disorders Victoria (EDV), The Melbourne Clinic (TMC),  and the Body Image and Eating Disorders Treatment and Recovery Service (BETRS) at the Austin Hospital (inpatient unit) and St Vincent’s Hospital (intensive day patient program), all in Melbourne, Victoria, Australia. Up to 30 mentees with an eating disorder (anorexia nervosa, bulimia nervosa, binge eating disorder or eating disorder not otherwise specified, according to the Diagnostic and Statistical Manual of Mental Disorders 5) will be matched with up to 30 mentors with a past history of an eating disorder. Participation will involve a longitudinal study assessing the efficacy of a peer mentor program for individuals with eating disorders. All mentees and mentors will be over the age of 18 years.

As this is a pilot proof-of-concept feasibility study, a randomised controlled trial will not be undertaken, but the program will be evaluated with a within-group design. Participation will involve a series of 13 mentoring sessions of up to 3 h each (ideally, every 2 weeks) over 6 months, following the mentee’s discharge from the BETRS/TMC inpatient unit or transition to/from the BETRS/TMC intensive eating disorders day program. The peer mentoring program will be delivered in a variety of community settings, i.e. local shopping centres, parks and cafes. Mentees and mentors will not be permitted to meet in either person’s home.

Mentors will be employed as ‘casual’ employees of EDV (see Additional file 1: Appendix A) and will be reimbursed for any reasonable expenses incurred during mentoring sessions as part of their employment, i.e. lunch for mentee and mentor, public transport fares for mentee and mentor practicing independent use of public transport, etc. Mentors and mentees will not receive any payment or reimbursement for this research.

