#### Eligibility criteria

Inclusion criteria for *mentees* include:Transitioning out of the BETRS inpatient program at the Austin Hospital or TMC, or transition in/out of the BETRS/TMC outpatient/day patient programCurrent diagnosis of an eating disorder (anorexia nervosa, bulimia nervosa, binge eating disorder or eating disorder not otherwise specified) according to the Diagnostic and Statistical Manual of Mental Disorders (DSM-5)Currently actively receiving treatment for their eating disorder for the duration of the program. (See Wellness Plan in Additional file 1: Appendix B). At a minimum, mentees must be receiving care from a GP and a psychologist.

Inclusion criteria for *mentors* include:Recovery from an eating disorder for a minimum of 2 years as indicated on the demographics and medical history form, in combination with the Eating Disorder Examination Questionnaire (EDE-Q). The wellness criteria are evidenced by self-reported absence of eating disorder symptoms (indexed by the EDE-Q), being weight-restored, not receiving treatment for eating disorders symptoms and use of a personal Wellness Plan/self-care activities to maintain their recovery. The Wellness Plan also outlines signs that indicate a mentor is struggling and how to best support them during these times.Successful recruitment as a staff member at EDV, including referee checks and agreement code of conduct

Exclusion criteria for mentors and mentees include anyone who is at serious risk of harm to oneself or another, as determined by the clinical team, for example, individuals at high risk of suicide.

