#### Quantitative assessments

The following quantitative measures will be collected at each time point to determine the efficacy of the peer mentor program for reducing eating disorder symptoms and quality of life:Clinical demographic and medical history questionnaire: Basic demographic information and a brief medical history will be collected at baseline. At other time points, changes to demographic information and medical history (e.g. new hospital admissions) will be recorded.Eating Disorders Examination Questionnaire (EDE-Q) [29]: The EDE-Q is a 28-item self-report measure of psychological constructs shown to be clinically relevant in individuals with eating disorders. This measure will be used to gather information about eating disorder symptomatology.Depression Anxiety Stress Scale (DASS-21) [30]: The DASS is a 21-item self-report instrument designed to measure the three related negative emotional states of depression, anxiety and tension/stress. Common comorbidities such as depression and anxiety [31] can impact outcomes as well as engagement and adherence and are important targets for intervention as well as being potential adverse outcomes which require monitoring and appropriate action if they reach concerning levels of risk.Brief Disability Questionnaire (BDQ) [32]: The BDQ is a self-report measure of disability in everyday activities and yields two main subscales: physical disability and mental health disability.Assessment of Quality of Life (AQoL) [33]: The AQoL is a self-report instrument that measures health-related quality of life.Feedback questionnaire (not at baseline): General feedback on the program will be sought.

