### Statistical methods

Quantitative analyses will include within-group analyses of variance (ANOVAs) and non-parametric assessments between time points, for mentees and mentors separately. Multiple imputation procedures that utilise the expectation-maximisation (EM) algorithm with bootstrap estimates of standard errors will be used for missing data. Using the six-stage approach described by Braun and Clarke [35], thematic analysis will be undertaken to identify key themes in the qualitative data.

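### The primary hypothesis of reduced relapse rates cannot be shown in a single group with current illness and no reference rate; relapse should be made descriptive

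*Protocol article*

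**What the plan says.** Under Primary hypotheses, the protocol article expects participation to improve symptoms and quality of life and to "reduce relapse rates in eating disorder participants". The Discussion again names relapse rates beside those two outcomes as part of what the trial will assess. The Study AIMS section names symptomatology and quality of life but not relapse as an outcome.

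On design, the section on study design and matching says that "a randomised controlled trial will not be undertaken, but the program will be evaluated with a within-group design". Under Eligibility criteria, mentees must have a current DSM-5 eating disorder diagnosis and be "Currently actively receiving treatment for their eating disorder for the duration of the program". Entry is at a transition: out of an inpatient unit, or into or out of an outpatient or day program.

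On measurement, the list of quantitative assessments has no item called relapse. The nearest is the medical-history form, where after baseline "changes to demographic information and medical history (e.g. new hospital admissions) will be recorded". The analysis section plans "within-group analyses of variance (ANOVAs) and non-parametric assessments between time points", for mentees and mentors separately.

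On a reference rate, the Background says only that treatment has limited efficacy, "often resulting in suboptimal recovery and high relapse rates". Its nearest figure is for recovery, in anorexia nervosa alone: "associated with long-term recovery rates of less than 50% among surviving patients".

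**The concern.** To say that a rate was reduced, one needs a second rate. It can come from a concurrent control group, from the same people before the intervention, or from an external source fixed in advance. The article provides none of the three for relapse.

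Two outcomes follow. Either this part of the primary hypothesis goes unanswered, or a relapse or readmission proportion is reported and then read as a reduction against some rate chosen once the result is known. The second matters more. The Discussion says the findings will inform larger randomised trials, and an unsupported statement that relapse fell would enter the case for those trials.

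**Working it through.** **Step 1: the plan's own figure.** The only quantitative justification is 28 participants per group for a moderate within-group effect, power 0.8, alpha 0.05. It reproduces for a continuous outcome. A one-group repeated-measures ANOVA with f = 0.25, three time points and an assumed correlation of 0.5 needs 28. A paired t-test with d = 0.5 needs 27 one-sided and 34 two-sided. Sidedness is a separate matter. What counts here is that no version contains a relapse rate, so the sample size gives no support to the relapse hypothesis.

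**Step 2: look for each possible comparator.**

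| Source of a comparison rate | What the article provides |
|---|---|
| Concurrent control group | None; single-group design |
| Baseline value in the same mentees | None; see step 3 |
| External or historical rate | None; relapse is called high without a figure, and the one percentage concerns recovery in one diagnosis |

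**Step 3: can a comparison between time points show a fall?** Take the possible readings of relapse in turn.

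- *An event after entry, such as readmission.* At baseline the cumulative proportion is 0/30 by construction. From 0 it can only stay level or rise at 3, 6 and 12 months. A comparison with baseline cannot show a reduction.
- *A state of active illness.* Mentees have a current diagnosis at entry and remission is not required. A later fall in the proportion who are ill would be remission or symptom improvement, which is already a separate part of the hypothesis.
- *Admissions after entry against admissions before entry.* The protocol does not plan this. For mentees enrolled on leaving inpatient or day-program care, recent intensive treatment is built into the earlier period by the entry criterion, so a fall would be likely without any program effect. For those stepping into a program the direction is not determined.

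**Step 4: what 30 mentees can deliver.** Inputs: n = 30 from the sample-size section; event counts x are assumed, because the article gives none. Exact (Clopper-Pearson) limits are the 0.025 quantile of Beta(x, n − x + 1) and the 0.975 quantile of Beta(x + 1, n − x).

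| Assumed events | Proportion | Exact 95% CI |
|---|---|---|
| 0/30 | 0% | upper limit 1 − 0.025^(1/30) = 11.6% |
| 6/30 | 20% | 7.7% to 38.6% |
| 9/30 | 30% | 14.7% to 49.4% |
| 12/30 | 40% | 22.7% to 59.4% |
| 15/30 | 50% | 31.3% to 68.7% |

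**Step 5: dependence on the unnamed reference.** Hold the assumed result at 9/30 and apply a two-sided exact binomial test against a range of assumed reference rates.

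| Assumed reference | 20% | 30% | 40% | 50% | 60% |
|---|---|---|---|---|---|
| p for 9/30 | 0.17 | 1.00 | 0.35 | 0.043 | 0.001 |

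The same data lie above the reference in the first column, on it in the second and below it in the last three, and are nominally significant in the last two. The choice of reference settles the conclusion.

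**The case against.** The article condenses a fuller protocol, and an analysis plan may exist. The definition of relapse and the test assigned to it could properly sit there. That stands, and this point does not rest on either being absent. A reader might infer from the analysis section that relapse is left out because ANOVA does not suit a binary outcome. The text does not support this, since it also plans non-parametric assessments between time points. Those remain within-group comparisons, however, and supply no comparator.

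Relapse can also be given a sensible meaning in these mentees. The article presents the program as helping people sustain recovery after specialist care, so deterioration or readmission after discharge is a meaningful event despite a current diagnosis. That stands too, and it is why a descriptive outcome is worth keeping. A meaningful event still has no baseline rate from which to fall.

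A reader might go further and say that admissions must fall after entry because everyone is selected on a recent treatment episode. The documents do not support that. Entry includes transition into a day program, the split between stepping in and stepping out is not given, and no before-after comparison is planned.

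Finally, this is openly a pilot with a within-group design. That is fair, and it limits the severity. It does not support keeping a directional primary hypothesis that the design cannot address.

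**Conclusion.** The point holds. As written, one named part of the primary hypothesis cannot be shown: there is no control group, no baseline relapse value and no stated reference rate. A definition of relapse supplied elsewhere would not create a comparator within this design. Only a justified external rate, fixed in advance, could.

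The event counts and reference rates in the working are assumptions used for illustration. A reader might infer that the wide intervals themselves rule out any conclusion about a reduction. They do not: an assumed 9/30 would differ clearly from a 60% reference. The missing reference is the defect, and interval width does not measure it.

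Nor does the point undermine the trial as a whole. The aims, the sample size and the feasibility criteria (80% completion, target recruitment within 2 years, adverse events) do not use relapse. It is a should-fix matter that limits what the trial may claim.

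**What to change.** 1. Remove the reduction in relapse from the primary hypotheses, and reword the Discussion so that relapse is described and not presented as an efficacy outcome.
2. Report the proportion of all enrolled mentees with a new eating-disorder hospital admission after baseline, by 6 and by 12 months, each with an exact 95% CI, from the medical-history form.
3. Do not count a planned transition into a day program as an event. Some mentees enrol at exactly that step, and the article names only hospital admissions as recorded.
4. State that neither this proportion nor a before-after comparison of admissions is evidence of a reduction, unless a justified external reference rate is named in advance.

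The cost is a change of wording and one hypothesis becoming descriptive. The form already records new hospital admissions; the team should confirm that its entries identify which admissions were for the eating disorder.
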